#### Aims and research questions

Our aim is to investigate whether CAMS represents improved services to patients with suicidal ideation and elevated suicidal risk in comparison to existing practices. The primary objective is to investigate whether treatment for suicidal patients by using CAMS results in a clinically and statistically significant reduction in suicidal thoughts and behaviors as compared to treatment as usual (TAU). Secondary aims are to investigate effects of CAMS and TAU upon mental health in general, symptom relief, and readmissions. Furthermore, we will test the influence of various moderating variables upon outcome, including qualities of the working alliance, the patients’ initial level of self-efficacy, and substance and alcohol abuse.

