#### Potential moderators and descriptive measures

The *Mini International Neuropsychiatric Interview (MINI)* will be used at baseline to identify DSM-VI and ICD-10 disorders associated with mood and psychosis along with other disorders. Studies have shown a good reliability and validity compared with the CIDI and the SCID-I interview [30]. In addition, the Structured Clinical Interview for DSM-IV Axis II Borderline Personality Disorder (SCID-II) will be administered to identify patients with borderline personality disorder given the importance of this group in the suicidality literature [31].

The *Generalized Self-Efficacy Scale (GSE)* is a reliable and valid measure comprising 10 items assessing the strength of an individual’s belief in the ability to respond to novel or difficult situations and to deal with a large variety of stressors [32, 33]. The GSE will be administered at baseline and after 6 and 12 months.

The *Working Alliance Inventory - ShortRevised (WAI-SR)* is a 12-item measure that will be used to assess the patient’s and therapist’s alliance after their third session together [34]. We will use the patient version of the instrument, which has high internal consistency and correlates well with other alliance measures.

Substance abuse is assessed with the *Alcohol Use Disorders Identification Test (AUDIT)* [35] and the *Drug Use Disorders Identification Test (DUDIT)* [36]. The AUDIT includes 10 questions about patterns of alcohol use and dependence. The DUDIT includes 11 questions about use or abuse of a list of drugs. Both instruments have satisfactory psychometric properties in clinical and non-clinical samples, with overall reliability above .80 and convergent validity, sensitivity, and specificity above 85 % [37, 38]. AUDIT and DUDIT will be scored at baseline.

The *Suicide Status Forms (SSFs)* are administered (initial, tracking, and outcome versions) as part of the course of care in CAMS (used for CAMS condition only). The SSF has six core rating assessments derived from theoretical approaches of Shneidman, Beck, and Baumeister and has well-established reliability and validity [39, 40].

As two of the measures (SSI-C and SASIC) did not have a Norwegian version, they were translated according to conventional procedures.

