There are no mandatory homework assignments during a CAMS course. The duration of CAMS care is dependent on the treatment progress and varies between patients. Treatment is concluded when adaptive coping skills are developed while the patient scores him/herself below 3 on subjective suicidal risk on the SSF during three consecutive CAMS sessions. Clinicians in the inpatient acute ward have reported that this criterion implies extended inpatient stays in the clinic, which is deemed unacceptable. Therefore, a deviation from the manual is necessary. However, when recruiting from the inpatient acute wards, we will aim to include those who are believed to stay for longer than only a couple of days and only those who are believed to be able to have at least three sessions with their allocated clinician after randomization. We will analyze all patients who have received three or more CAMS sessions.

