### Statistical analysis

We will use generalized linear regression to examine the effects of treatment condition (CAMS versus TAU) upon suicidal thoughts (SSI-C scores) and mental health functioning (OQ-45 scores). Possible moderator effects will be estimated by using an array of covariates, including baseline measures (age, gender, ethnicity, diagnoses, and psychological measures), working alliance, medication during the treatment period, varying treatment length, new treatments delivered during follow-up, and an eventual leakage of CAMS elements into TAU.

Statistical analysis will be by intention to treat. To manage and replace missing data, we will create several sets of plausible imputed data, based on the Bayesian approach, by using multiple imputation procedures for the variables of interest, following the guidelines of Sterne and colleagues [43]. In a further sensitivity analysis we will perform the analysis using the per protocol method, excluding patients who did not complete treatment or missed measurements.

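### Five variables that arise after randomisation are planned as moderators, so those moderator results would not be protected by randomisation

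*Protocol article*

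**What the plan says.** The Statistical analysis section of the protocol article first states the effect model: "We will use generalized linear regression to examine the effects of treatment condition (CAMS versus TAU) upon suicidal thoughts" and on OQ-45. A separate sentence follows: "Possible moderator effects will be estimated by using an array of covariates". The covariates named there begin with baseline measures (age, gender, ethnicity, diagnoses, psychological measures) and continue with "working alliance, medication during the treatment period, varying treatment length, new treatments delivered during follow-up, and an eventual leakage of CAMS elements into TAU". The next paragraph adds: "Statistical analysis will be by intention to treat".

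Moderation is a stated aim. Under Aims and research questions: "we will test the influence of various moderating variables upon outcome, including qualities of the working alliance". Self-efficacy is named there by its initial level; alliance is not. Under Potential moderators and descriptive measures, the alliance inventory is used to "assess the patient’s and therapist’s alliance after their third session together". The CAMS intervention section says: "The duration of CAMS care is dependent on the treatment progress and varies between patients".

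**The concern.** A moderator has to be fixed before allocation, or at least be something that allocation cannot change. An arm-by-covariate term then compares like with like within each level of the covariate. If treatment or response can shift the covariate, patients at the same level in the two arms were sorted there by different processes, and the interaction mixes effect modification with selection.

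The moderation aim is what is directly at stake. A reader could be told that CAMS works better with a strong alliance, or in longer treatments, when the pattern reflects who reached that level under each treatment. A true pattern could equally be masked.

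**Working it through.** **1. The plan's own figure.** No figure is attached to the moderator analysis. The nearest is the power calculation: difference 4, SD 7, 40 per arm, one-sided alpha 0.05. SE = 7 × √(2/40) = 1.565. Power = Φ(4/1.565 − 1.645) = Φ(0.911) = 81.9%, against the stated 82%. Enrolment = 80/0.80 = 100. Both reproduce.

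**2. Can allocation or response change each variable?**

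| Variable | What the protocol article says elsewhere | Status |
|---|---|---|
| Working alliance | CAMS is meant to build it (The CAMS approach); measured after session three, at T2 (Table 1) | Candidate mediator |
| Treatment length | Depends on progress in CAMS (CAMS intervention); no such rule stated for TAU | In CAMS partly a response measure; different meaning by arm |
| New treatments in follow-up | Discharged non-responders are pointed towards possible re-referral (Removal from the trial, safety monitoring, and acceptability) | Can follow from outcome |
| Medication during treatment | Given as needed in TAU (TAU intervention) | After randomisation; no text shows that CAMS changes it, none excludes it |
| Leakage into TAU | Defined in one arm | Always zero in CAMS |

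**3. Arm-by-leakage.** Take E(Y) = β0 + β1·A + β2·L + β3·A·L, with A = 1 for CAMS. L = 0 whenever A = 1, so A·L = 0 for everyone. The design matrix has rank 3 with 4 columns, and β3 does not exist.

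**4. What would follow if such a variable entered the effect model.** This is conditional, and every input is assumed. Let CAMS shift alliance by d SD, let alliance be worth b BSSI-C points per SD, and let unmeasured severity act on alliance (c) and on outcome (g). With a total effect of −4, the adjusted arm coefficient is −4 − (b + g·c)·d. The true direct effect is −4 − b·d. The simulated column comes from 400,000 patients with SD 7.

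| d | b | g·c | Direct | Adjusted (formula) | Adjusted (simulated) |
|---|---|---|---|---|---|
| 0.3 | 0 | 0 | −4.0 | −4.00 | −4.02 |
| 0.3 | −2 | 0 | −3.4 | −3.40 | −3.43 |
| 0.6 | −3 | 0 | −2.2 | −2.20 | −2.20 |
| 0.3 | 0 | 3 × −0.5 | −4.0 | −3.55 | −3.56 |
| 0.6 | 0 | 3 × −0.5 | −4.0 | −3.10 | −3.13 |
| 0.3 | −2 | 3 × −0.5 | −3.4 | −2.95 | −2.96 |
| 0.6 | −3 | 3 × −0.5 | −2.2 | −1.30 | −1.30 |

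Rows four and five have no mediation, so their shift is pure collider bias. In power terms, an assumed mediated share of 10%, 25% or 50% leaves 3.6, 3.0 or 2.0 points. With SD kept at 7, power is then 74.4%, 60.7% or 35.7%.

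*Later treatment.* If its log-odds rise by 1 or 2 per 7 outcome points, the adjusted coefficient is −3.3 or −2.5.

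*Leakage.* If a fraction p of TAU receives a share s of the CAMS effect at random, the intention-to-treat contrast is −4 + 4·p·s. That gives −4 + 4(0.10)(0.5) = −3.8 and −4 + 4(0.25)(1) = −3.0. Adjusting for leakage gave −4.0 when leakage was unrelated to severity, and about −3.6 to −3.9 when sicker TAU patients were more likely to receive it. In all eight settings adjustment moved the estimate away from zero.

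**5. Are the remaining candidates pre-allocation?** The Recruitment section puts BSSI-C before randomisation and the other baseline measures after it, so GSE, AUDIT and DUDIT are not strictly pre-randomisation. Diagnoses are inconsistent: the MINI is placed at baseline under Potential moderators and descriptive measures, but at T2 in Table 1, and Assessments and measurements places the diagnostic interview at T2, after inclusion.

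**The case against.** The strongest reply is that the effect model and the moderator sentence are separate, and that the analysis is declared intention to treat. A reader might infer that the reported CAMS effect will be adjusted for alliance, treatment length and the rest, and so partly removed. The text does not say that. Nor does it exclude it, but the choice of covariates for each model is commonly left to an analysis plan that is not shown. This part of the objection stands, and the harm to the main estimate must remain conditional.

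Other parts also stand. The calculations in step 4 concern an arm coefficient, not an interaction, so they do not size a false moderator. The alliance inputs include strong ones, and weaker ones lose little (3.4 of 4 points in the second row of the table). The bias has no common direction, given the leakage result. The CAMS ending criterion uses self-rated risk on the SSF and coping skills, not BSSI-C, and the acute wards deviate from it, so length is not simply a proxy for the outcome. Re-referral is only possible, not automatic. No text shows that CAMS alters medication.

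What the reply does not answer is that the article itself names these variables as moderators and makes alliance moderation an aim. That is a stated choice, not a detail left for later.

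**Conclusion.** The concern holds for the moderator analysis. Variables that treatment or response can change are not valid moderators, and the protocol's own text shows this possibility for alliance, CAMS treatment length and later treatment. Medication during treatment is likewise measured too late to be assumed unaffected. The leakage interaction is impossible as a matter of design, with no assumption needed.

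No numerical size can be given for a false or masked interaction, because the documents give neither its form nor its inputs. The 1.3 to 4.0 point range for alliance adjustment applies only if alliance entered the model for the CAMS effect, and it rests wholly on the assumed mediation and confounding. The documents do not support a claim that the planned primary comparison is biased. This is a defect in a stated secondary aim that should be corrected.

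**What to change.** - Limit moderator tests to variables fixed before allocation: age, gender, ethnicity, treatment unit, baseline BSSI-C, and diagnoses already in the patient record.
- Include GSE, AUDIT and DUDIT only if they are completed before allocation is disclosed, and say so.
- State that the model for the CAMS effect excludes the five post-randomisation variables.
- Analyse alliance as an exploratory mediator, with its assumptions written down.
- Report medication, treatment length and later treatments descriptively by arm.
- Handle leakage in a separate exploratory contamination analysis.
- Reconcile the timing of the diagnostic interview across Table 1, Assessments and measurements, and Potential moderators and descriptive measures.

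The change to the five variables is one of wording and needs no new data. Keeping GSE, AUDIT and DUDIT as moderators may require a change in the order of baseline procedures. The price is fewer moderators to report.

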### Power calculation

In calculating power, we use one-sided confidence intervals because previous studies have indicated CAMS to be superior to TAU [18, 23–25]. We use the following assumptions: (1) the main outcome variable BSSI-C score after treatment — which is scored on a 0–38 point scale — has a standard deviation of 7 points [27]; (2) there are equal sample sizes in the experimental and control groups; (3) a four-point difference in BSSI-C scores at follow-up will represent a meaningful clinical difference between CAMS and TAU; and (4) the alpha level is 0.05. Based on these assumptions, 82 % power will be achieved by including 80 participants in the trial, who will be randomized to CAMS or TAU. Assuming a 20 % drop-out rate, our desired sample size is 100 participants at inclusion.

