### Selection bias after all?

One may question whether our patient population is preselected. At the outset, all patients who present with moderate to severe suicidal thoughts, plans, and behaviors are eligible to participate in the project. However, most suicidal patients receiving treatment in our clinic are not invited to participate. An array of factors may explain why, and in the end may serve as a selection bias. Recruitment difficulties as discussed above may be one factor. A low general capacity or opportunity to include new patients and perform the randomization procedure is another. The study’s low representation of therapists at each of the participating departments and sites in our services limits the rate of inclusion. One could ask whether a particular group of well-functioning patients is more often invited to participate and more eligible to accept attendance in the research project. Moreover, as this study demands an informed consent to participate, those with the more severe forms of depression and psychosis are not included.

Even though our inclusion criteria are wide, our services as a whole do not offer treatment to all patients who are referred. One group who might be denied treatment within our facilities consists of people who suffer from suicidal problems and ideation but who are considered not to have the “right to necessary health care,” a judicial term and principle that guides selection of those who are to receive treatment within specialized care in Norway. This declined group may include people with chronic psychiatric and psychosocial problems with multiple previous unsuccessful treatment attempts. This group is usually referred to local community health centers.

Another group who does not receive treatment is those who for different reasons decline treatment and follow-up from the specialized health care system after a suicide attempt.

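### The one stated sensitivity analysis, per protocol without patients who missed measurements, cannot probe outcome-related drop-out, and no other stated analysis does

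*Protocol article*

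**What the plan says.** The Statistical analysis section sets the analysis principle in one sentence: "Statistical analysis will be by intention to treat". Missing values are then handled by imputation: "To manage and replace missing data, we will create several sets of plausible imputed data", "by using multiple imputation procedures for the variables of interest". The section does not name the missingness assumption behind the imputation. It goes on: "In a further sensitivity analysis we will perform the analysis using the per protocol method", and defines that set as "excluding patients who did not complete treatment or missed measurements". No other sensitivity analysis is named.

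Three other places bear on this point:

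- **Power calculation.** Loss is allowed for in the sample size: "Assuming a 20 % drop-out rate, our desired sample size is 100 participants at inclusion". The rate is not split by arm.
- **CAMS intervention.** Treatment concludes once coping skills have developed and the patient has rated suicidal risk below 3 on the SSF in three consecutive sessions. A departure from this rule is accepted on acute inpatient wards. The section also plans an analysis of patients with at least three CAMS sessions.
- **TAU intervention.** Treatment is not manualised, and no comparable rule for concluding it is given.

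**The concern.** Standard multiple imputation is valid when missing patients resemble observed patients with the same recorded data (missing at random). The main threat to that in this trial is that a patient's current suicidality, which goes unrecorded once the interview is missed, drives the loss. A useful sensitivity analysis would relax that assumption. The stated one removes everyone with a missed measurement, which generally tightens it.

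The second exclusion adds a separate problem. If completion has the meaning given in the CAMS intervention section, removing non-completers takes out CAMS patients who stayed suicidal, with no matching filter in TAU. The Removal from the trial section also lets therapists end treatment that they judge inadequate or harmful, and those patients would presumably count as non-completers too. The per-protocol contrast may then lean towards CAMS. The analysis of patients with three or more CAMS sessions also selects on treatment received and does not fill the gap.

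The risk is that a positive result is reported as robust because it survived a check that could not have detected the problem.

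**Working it through.** **Inputs from the Power calculation section.** SD 7 points, target difference 4 points, one-sided alpha 0.05, equal arms, 80 evaluable patients (40 per arm), 20% drop-out.

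**Reproducing the plan's figures.**
- SE = 7 × √(2/40) = 1.565.
- Power = Φ(4/1.565 − 1.645) = 0.819, which matches the stated 82%.
- Sample size = 80/0.8 = 100, as stated.

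**Effect of hidden worsening.** Let p be the fraction missing in an arm and δ the points by which its missing patients are worse than imputed. The arm difference shifts by p(CAMS) × δ(CAMS) − p(TAU) × δ(TAU). The δ values are my assumptions; 7 is one SD. SE is held at 1.565. With 20% missing per arm and worsening in one arm only:

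| δ | Shift = 0.2 × δ | Share of 4 points | Error if no true effect, worsening in CAMS | Power at a true 4 points, worsening in TAU |
|---|---|---|---|---|
| 2 | 0.4 | 10% | about 8% | about 74% |
| 4 | 0.8 | 20% | about 13% | about 66% |
| 7 | 1.4 | 35% | about 23% | about 51% |

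Error = 1 − Φ(1.645 − shift/1.565). Power = Φ((4 − shift)/1.565 − 1.645).

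- **Equal loss and equal δ in both arms:** 0.2δ − 0.2δ = 0, so no shift.
- **Unequal loss, same δ in both arms (assumed 10% against 30%):** 0.2δ in size, so again 0.4, 0.8 or 1.4 points.

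**Tipping point.** The critical difference is 1.666 × 1.565 = 2.61 (one-sided t, 78 degrees of freedom). An imputed difference of 4 loses significance at a CAMS-only δ of (4 − 2.61)/0.2, about 7 points. It reaches zero at 4/0.2 = 20 points.

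**Do the two planned approaches diverge when they should?** This was checked with a large simulation: true difference −4, SD 7, assumed baseline–outcome correlation 0.5, 18% to 19% missing. Unadjusted complete cases were compared with imputation from baseline within arm.

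| Drop-out depends on | Complete cases | Imputation |
|---|---|---|
| Baseline, in opposite directions by arm | −4.98 | −4.00 |
| The outcome itself, in CAMS only | −5.00 | −4.77 |

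In the first row, exclusion is biased where imputation is not, so it needed the stronger assumption. In the second, both overstate the benefit, by 1.00 and 0.77 points, and lie closer to each other than either lies to the truth. The simulation covers only the exclusion for missed measurements, not the exclusion of treatment non-completers.

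**The case against.** The strongest reply is that this is a condensed article. It states intention to treat, multiple imputation and a per-protocol set. The missingness assumption and any delta analysis are usual content of a statistical analysis plan that is not shown. Calling the per-protocol analysis a further one does not exclude others, and the article nowhere says that it is meant to test the imputation.

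Part of this stands. A reader might infer that outcome-related drop-out is never tested in this trial. The document supports only that no stated analysis tests it. But the point does not rest on silence. The article does choose a sensitivity analysis, names it directly after the imputation, and defines it partly by missed measurements. That stated choice cannot do the job.

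Four further limits stand:

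- A reader might take the remark under Selection bias after all? about people who "decline treatment and follow-up from the specialized health care system after a suicide attempt" as evidence of drop-out. It describes people who refuse specialised care and so never enter the trial, and says nothing about loss of enrolled patients.
- Exclusion usually assumes more than imputation, but not always. A complete-case regression adjusted for every predictor of missingness can be as valid as imputation from the same variables, and the article does foresee covariates. Bias in the same direction is likewise not guaranteed, since removing non-completers can move the estimate either way.
- The tabulated figures put all the hidden worsening in one arm, which is the extreme case.
- Registry data on suicide attempts, admissions and death do not depend on research interviews, so serious events in drop-outs are not wholly unseen. They do not replace BSSI-C.

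**Conclusion.** The point holds in this form: the stated sensitivity analysis generally assumes more than the main analysis, selects on treatment completion in a way that may differ by arm, and so gives no reassurance about outcome-related drop-out. It should be changed.

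The size is moderate and illustrative. With 20% missing and one-arm worsening of 2 to 7 points, the contrast moves by 0.4 to 1.4 points. A reader might infer that the primary result would be overturned. The figures do not show that: a full 4-point difference withstands a CAMS-only shift of up to about 7 points, and smaller observed effects would tip sooner.

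The conclusion rests on 20% being a planning allowance rather than observed loss, on chosen δ values, on SE held at 40 per arm, and on outcome-related loss being plausible rather than documented. The lean towards CAMS also requires that completion take the meaning given in the CAMS intervention section.

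**What to change.** - Keep intention to treat with multiple imputation as the main analysis, and state that it assumes data missing at random.
- Label the per-protocol analysis supplementary, and do not present it as a check on missing data.
- As the missing-data sensitivity analysis, use delta-adjusted multiple imputation: add 0 to 7 points to imputed BSSI-C values in CAMS only, in TAU only, and in both arms. Report the delta at which the conclusion changes.

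The cost is a few lines of text and a slightly longer analysis that reuses the planned imputed data sets. No new data are needed, and sample size and power are unchanged. The Assessments and measurements section keeps data on paper until all follow-up interviews are done, so the change can be fixed before data entry. The downside is that a positive result may prove fragile.
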